#### Exclusion criteria

2.2.3

1.Is undergoing systemic sex hormone therapy;2.Combined with other active respiratory diseases, such as asthma, structural defects of the upper respiratory tract, etc.3.Wearing hearing AIDS, unable to cooperate with the treatment;4.EAP was used to treat other respiratory diseases in the past 6 months;5.Allergic to therapeutic devices (e.g., tape, steel balls).

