#### Inclusion criteria

2.2.2

The patient was diagnosed with allergic rhinitis, and the diagnostic criteria refer to the 2008 WHO diagnostic description of allergic rhinitis,^[8]^ aged from 18 to 70 years, had at least 2 years history of typical allergic rhinitis symptoms, and had a positive reaction to any common allergen of allergic rhinitis.

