### Randomization and blinding

2.3

In accordance with the principle of random distribution, the patients were randomly divided into treatment group (Real EAP group) and control group (Sham EAP group) by using computer-generated random number table. The designers and acupuncturists of this study are aware of the grouping due to the limitation of treatment. Participants and subjects involved in recruitment, evaluation, data entry, and data analysis were not informed of the grouping.

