### Intervention method

2.4

During the 8-week treatment period, participants received Real EAP or Sham EAP treatment once a week, and all treatments will be performed by the same registered acupuncturist (>5 years of treatment experience) to ensure participant-blinded and treatment consistency. Before the first treatment, the acupuncturist will provide the patient with technical information about the EAP and advise the patient on precautions. Points will be swabbed with 70% isopropyl alcohol before attaching the stainless steel pellets (1.2 mm in diameter, TaiHe, China), participants were asked to gently press the ball three times a day (morning, noon, and evening) to promote acupoint stimulation. Press each pellets for about 10 s, or until the ear turns red or slightly sore. In the subsequent treatment, the acupuncturist removed the previous treatment pellets once a week, and repeated the same steps on the other ear. There will be no skin penetration.

Five acupoints will be used for real EAP; these include shenmen (TF_4_), internal nose (TG_4_), lung (CO_14_), wind stream (SF_1,2i_), and adrenal gland (TG_2p_). They are selected on the basis of traditional Chinese medicine theory, previous clinical research, and expert consultation.^[16,20]^ Five sham EAP acupoints are helix 2 (HX_10_), shoulder (SF_4,5_), clavicle (SF_6_), OCCIPUT (AT_3_), and tooth (LO_1_). These acupoints have no effect on the relief of allergies or any nasal symptoms.

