## Discussion

3

Allergic rhinitis is often induced by weather changes, pollen, animal hair, diet and other allergic factors, the main clinical manifestations are continuous episodes of paroxysmal sneezing, a large number of watery snot, nasal congestion and itching, and some patients have decreased sense of smell, affecting the quality of life.^[22]^ AR is an allergic reaction mediated by IgE under the chemotaxis of various inflammatory cytokines after specific individual contact with antigen. The nasal mucosa produces various pathological changes, and the excitability of the nasal parasympathetic nerve is too strong, resulting in vascular dilation, enhanced permeability, excessive secretion of serous cells,^[23]^ modern medicine is mainly based on drug treatment, Medications include oral and topical histamine H1 receptor antagonists, topical and systemic glucocorticosteroids, chromones, decongestants, topical anticholinergics, antileukotrienes, and oral anti-allergic drugs.^[24]^ However, the adverse reactions caused by it are still a common concern of doctors and patients, and the curative effect is limited, unable to completely relieve the symptoms^[25]^ Therefore, it is necessary to find alternative treatment options for patients with allergic rhinitis.

Ear acupuncture has the characteristics of simple operation, less pain, less side effects and lasting and stable effect. Clinical studies have proved that lung (CO_14_) and wind stream (SF_1,2i_) can relieve congestion and runny nose, adrenal gland (TG_2p_) can resist inflammation and allergy, and its mechanism of action may be to regulate the imbalance of Th1/Th2 cells by inhibiting the differentiation of Th cells to Th2, thereby reducing the synthesis of IgE and inhibiting the occurrence of allergic reactions.^[26]^ Although EAP has been widely used in the treatment of allergic rhinitis in China, there is still a lack of strict clinical studies to verify its curative effect. The existing clinical studies mostly use EAP combined with other treatment schemes, or compare the curative effect with western medicine, and many confounding factors interfere with our evaluation of its curative effect.^[27,28]^ Therefore, we designed this randomized controlled study to determine the efficacy of EAP in the treatment of allergic rhinitis by comparing with sham EAP.

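### Exclusion 4 bars recent ear acupuncture given for other respiratory diseases but, as worded, admits patients recently treated with it for allergic rhinitis, who may recognise the sham

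*Protocol article*

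**What the plan says.** Section 2.2.3 lists five exclusions. The fourth is "EAP was used to treat other respiratory diseases in the past 6 months". The second is "Combined with other active respiratory diseases, such as asthma, structural defects of the upper respiratory tract, etc". Section 2.2.2 asks that the patient "had at least 2 years history of typical allergic rhinitis symptoms" and sets no limit on earlier EAP.

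On blinding, section 2.3 states: "Participants and subjects involved in recruitment, evaluation, data entry, and data analysis were not informed of the grouping". Section 2.4 gives five points for real EAP and five for sham, and has participants press the pellets three times a day. Section 2.5 makes the fall in a self-assessed total nasal symptom score the main outcome.

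The Discussion says that "EAP has been widely used in the treatment of allergic rhinitis in China" and credits the technique with "less side effects and lasting and stable effect".

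**The concern.** The evident purpose of exclusion 4 is to keep out people with recent experience of the study treatment. As worded, it misses the experience most relevant here. Someone treated for asthma five months ago is excluded; someone treated for allergic rhinitis last week is not.

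The second person is the one more likely to have had pellets at rhinitis points and to notice when they are placed elsewhere. A participant who concludes that the treatment is sham may report less improvement, and one who recognises familiar sites may report more. Both push the self-rated difference in favour of real EAP. The acupuncturist knows the allocation, so participant blinding is the main protection for this outcome.

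**Working it through.** No figure in the plan belongs to this point, so the check is a reading of the text, followed by a note on size.

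**1. What *other* means.** Exclusion 2 uses *other* for active respiratory diseases besides allergic rhinitis; it must, since every participant has allergic rhinitis. The same word in the same list, two items later, carries the same meaning. Exclusion 4 therefore does not reach EAP given for allergic rhinitis.

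**2. Whether another criterion closes the gap.** The inclusion criteria cover diagnosis, age, symptom history and allergen reactivity. The remaining exclusions cover hormone therapy, concurrent respiratory disease, hearing aids and allergy to the device materials. None concerns earlier EAP.

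**3. Whether such patients are plausible.** At least 2 years of symptoms leaves time for earlier treatment, and the Discussion describes EAP for this disease as common in China. The article gives no proportion.

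**4. Whether they could tell the arms apart.** The point sets in section 2.4 are:

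| Arm | Points |
|---|---|
| Real | TF4, TG4, CO14, SF1,2i, TG2p |
| Sham | HX10, SF4,5, SF6, AT3, LO1 |

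No point is shared (0 of 5), although two sham points carry the same SF prefix as one real point. Participants press each pellet three times a day and record daily how many remain attached (section 2.5), so they know where the pellets sit.

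**5. Size.** The planned difference in section 2.2.1 is 3.47 − 2.82 = 0.65 points. Any bias from recognition would be roughly

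bias = share of participants who recognise their arm × shift in the real-minus-sham difference among them.

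The documents give neither term, so the product cannot be computed.

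For dilution by carry-over, only an assumed range can be shown. The pooled SD is √((1.48² + 1.57²)/2) = 1.526. The test is a two-sided t test at 0.05 with the stated 107 per group:

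| Assumed shrinkage of 0.65 | Difference | Power |
|---|---|---|
| 0% | 0.650 | 87% |
| 5% | 0.618 | 84% |
| 10% | 0.585 | 80% |
| 20% | 0.520 | 70% |
| 30% | 0.455 | 58% |

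These shrinkages are assumptions, with the SD held fixed, and the finding does not rest on them.

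**The case against.** **The wording may be a translation slip** for allergic rhinitis or other respiratory diseases. That is possible, but nothing in the article corrects it, and screening staff would apply the line as written.

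**Recognition is not shown.** Nothing says that earlier EAP for rhinitis used these five points or that patients would remember them. Both arms have five points, the same pellets, the same pressing routine and the same acupuncturist. This stands as a limit: recognition is a plausible risk, not a demonstrated effect.

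**Carry-over.** From the claim of a lasting effect, a reader might infer a bias that cannot be repaired. The documents do not support that. Allocation is random, so earlier users fall evenly between arms on average; the outcome is a decrease in score; and a record of earlier EAP would allow adjustment.

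**Other indications.** The Introduction says that EAP is also used for insomnia, obesity and pain, and a reader might infer that those patients are an equal threat. Nothing in the article suggests that they would recognise rhinitis points or carry over a nasal effect.

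**A tempting figure.** If 10% to 20% of participants recognised their arm and the difference among them shifted by 1 point, the bias would be 0.10 to 0.20, or 0.10/0.65 = 15% to 0.20/0.65 = 31% of the planned difference. Both inputs are invented, and a 1-point shift is 1/0.65 = 1.5 times the whole planned difference. The range carries no evidential weight.

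**Matters that do not bear on the criterion.** The acupuncturist's knowledge of allocation is disclosed, and the lack of double blinding is acknowledged as a limitation. Before the first session, "the acupuncturist will provide the patient with technical information about the EAP", but no difference by arm is described. The absence of a question on perceived allocation is not an error in a condensed article.

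**Conclusion.** The point holds in a limited form. Exclusion 4 is too narrow for its evident purpose: it admits patients who had EAP for allergic rhinitis in the past 6 months. With different sham sites, pellets handled by the participant and a self-rated primary outcome, this creates a directional risk to participant blinding.

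The size is unknown. The conclusion rests on reading *other* consistently within the list, and on the assumption that at least some recently treated patients would notice the change of sites. Carry-over is secondary and would mainly add noise or dilute the contrast. The text does not show that blinding will fail, that the result will be biased by any stated amount, or that EAP for unrelated conditions must be excluded.

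**What to change.** Reword exclusion 4 so that it covers EAP for allergic rhinitis as well as for other respiratory diseases, keeping the protocol's own 6-month window.

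Record any other earlier EAP (older than 6 months, or for another indication) at baseline, so that it can serve as a covariate or define a sensitivity analysis of the primary outcome.

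Optionally, ask participants at the end of treatment which treatment they believe they received. This helps in reading the result but does not repair the criterion.

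The cost is one eligibility line, one baseline item, perhaps one further case report form question, and slightly fewer eligible patients.

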### Randomization and blinding

2.3

In accordance with the principle of random distribution, the patients were randomly divided into treatment group (Real EAP group) and control group (Sham EAP group) by using computer-generated random number table. The designers and acupuncturists of this study are aware of the grouping due to the limitation of treatment. Participants and subjects involved in recruitment, evaluation, data entry, and data analysis were not informed of the grouping.

### Intervention method

2.4

During the 8-week treatment period, participants received Real EAP or Sham EAP treatment once a week, and all treatments will be performed by the same registered acupuncturist (>5 years of treatment experience) to ensure participant-blinded and treatment consistency. Before the first treatment, the acupuncturist will provide the patient with technical information about the EAP and advise the patient on precautions. Points will be swabbed with 70% isopropyl alcohol before attaching the stainless steel pellets (1.2 mm in diameter, TaiHe, China), participants were asked to gently press the ball three times a day (morning, noon, and evening) to promote acupoint stimulation. Press each pellets for about 10 s, or until the ear turns red or slightly sore. In the subsequent treatment, the acupuncturist removed the previous treatment pellets once a week, and repeated the same steps on the other ear. There will be no skin penetration.

Five acupoints will be used for real EAP; these include shenmen (TF_4_), internal nose (TG_4_), lung (CO_14_), wind stream (SF_1,2i_), and adrenal gland (TG_2p_). They are selected on the basis of traditional Chinese medicine theory, previous clinical research, and expert consultation.^[16,20]^ Five sham EAP acupoints are helix 2 (HX_10_), shoulder (SF_4,5_), clavicle (SF_6_), OCCIPUT (AT_3_), and tooth (LO_1_). These acupoints have no effect on the relief of allergies or any nasal symptoms.

### Outcome measures

2.5

The main outcome indicator is the decrease of Total nasal symptom score^[19]^ (including self-assessment in several aspects of nasal congestion, runny nose, nasal itching, sneezing, difficult sleep). The secondary outcome indicators are Standardized Rhinoconjunctivitis Quality of Life Questionnaire (RQLQ)^[21]^ and mitigate changes in drug use. Data were recorded by Case Report Forms (CRFs) during treatment (8 weeks, weekly) and follow-up (12 weeks, every 3 weeks). Considering the possibility of pellets falling off during treatment, participants were asked to record how many pellets were still attached to their auricular points in the CRFs every day. The total number of pellets remaining each week was analyzed as treatment dose data.

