#### Participants source and sample size estimation

2.2.1

We will include patients through pre-hospital recruitment and screening of inpatients. After qualification assessment, patients will be informed of the protocol and purpose of the trial, and will be included in the study only after consenting to the study and signing an informed consent form.

Sample size estimation will be based on post-treatment Total nasal symptom score.^[19]^ According to the pre-experiment results, the real EAP group was 2.82 ± 1.48, and the Sham EAP group was 3.47 ± 1.57, α = 0.05, β = 0.2, and 107 samples were needed in each group according to the calculation by PASS15.0 software. Consider a drop-out rate of no more than 20%, with 134 cases in each group.

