### Statistical analysis

2.8

The data were analyzed by SPSS.22 software package, the hypothesis test was two-tailed test, and the α level was set to *P* < .05. The measurement data in accordance with normal distribution and homogeneity of variance are tested by independent sample *T* test, while those inconformable are tested by Mann–Whitney *U* test.

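### The trial is sized on the post-treatment nasal symptom score, but the main outcome is the decrease, tested unadjusted: the 80% power is not established for that outcome, and baseline adjustment would add precision

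*Protocol article*

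**What the plan says.** Three sections of the protocol article bear on this.

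- **Outcome measures (2.5)** makes the primary variable a change from baseline: "The main outcome indicator is the decrease of Total nasal symptom score".
- **Participants source and sample size estimation (2.2.1)** uses a different variable: "Sample size estimation will be based on post-treatment Total nasal symptom score". The inputs come from a preliminary experiment: "the real EAP group was 2.82 ± 1.48, and the Sham EAP group was 3.47 ± 1.57". The result is "α = 0.05, β = 0.2, and 107 samples were needed in each group", which becomes "with 134 cases in each group" after an allowance of up to 20% for drop-out.
- **Statistical analysis (2.8)** is two-sided at 0.05. For the comparison of arms it states "The measurement data in accordance with normal distribution and homogeneity of variance are tested by independent sample" t test, with the Mann–Whitney U test where those conditions fail. No other test and no covariate is named.

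The article gives no SD of the decrease, no baseline SD and no correlation between baseline and post-treatment scores.

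**The concern.** A sample size carries its power only for the variable whose SD went into it. The SD of a decrease depends on the baseline SD and on the baseline-to-post correlation as well as on the post-treatment SD, so it can be larger or smaller than the post-treatment SD. The power claimed in 2.2.1 therefore cannot be carried over to the outcome in 2.5 without a figure that the article does not give.

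There is a second consequence. A two-sample test on the decrease uses the baseline score with a fixed weight of one. Regression on baseline estimates the weight from the data and is normally more precise. The trial must already hold the baseline score to compute a decrease, so the extra precision is available and is not being used.

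**Working it through.** **Inputs from the article.** Means 2.82 and 3.47, SDs 1.48 and 1.57, β = 0.2 and 107 per group (2.2.1); two-sided α = 0.05 (2.8).

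**Step 1: the article's own figure.**
- Difference = 3.47 − 2.82 = 0.65.
- Pooled SD = √((1.48² + 1.57²)/2) = √2.328 = 1.526.
- Standardised difference = 0.65/1.526 = 0.426.
- n per group by normal approximation = 2(1.960 + 0.842)²/0.426² = 87. By the noncentral t distribution it is 88, pooled or Welch.

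The stated 107 is not reproduced. With 107 per group, power for the post-treatment score is about 87%. The drop-out step does reproduce: 107/0.8 = 133.75, so 134.

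**Step 2: variances for the outcome that is declared primary.** Write s₀ and s₁ for the baseline and post-treatment SDs.
- Unadjusted decrease: s₀² + s₁² − 2r·s₀s₁.
- ANCOVA on baseline: s₁²(1 − r²).
- Difference between the two: (s₀ − r·s₁)², which is never negative and is zero only when the regression slope on baseline, r·s₁/s₀, equals 1.
- The decrease is noisier than the post-treatment score when r < s₀/(2s₁).

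**Step 3: a working assumption.** The article gives neither s₀ nor r. Take s₀ = s₁ = 1.526 and equal expected baseline means, so that the difference in decrease is also 0.65, and let r range. Then SD of decrease = 1.526·√(2(1 − r)), ANCOVA SD = 1.526·√(1 − r²), and the variance ratio is 2/(1 + r). Power is by noncentral t with 107 analysed per group.

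| r | SD, decrease | Power, decrease | n/group for 80% | SD, ANCOVA | Power, ANCOVA | n/group for 80% | Variance ratio |
|---|---|---|---|---|---|---|---|
| 0 | 2.158 | 59% | 174 | 1.526 | 87% | 88 | 2.00 |
| 0.3 | 1.805 | 75% | 123 | 1.455 | 90% | 80 | 1.54 |
| 0.4 | 1.671 | 81% | 105 | 1.398 | 92% | 74 | 1.43 |
| 0.5 | 1.526 | 87% | 88 | 1.321 | 95% | 66 | 1.33 |
| 0.6 | 1.365 | 93% | 71 | 1.221 | 97% | 57 | 1.25 |
| 0.7 | 1.182 | 98% | 53 | 1.090 | 99% | 46 | 1.18 |

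**Step 4: break-even.** With 107 per group, 80% power needs an SD of 1.689. Setting 2(1 − r) = (1.689/1.526)² = 1.225 gives r ≈ 0.39. Under equal SDs the decrease and the post-treatment score are equally noisy at r = 0.5. The break-even for 80% lies below 0.5 only because 107 exceeds the 88 that the stated inputs require.

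**Step 5: one analysis covers both variables.** Let decrease D = B − P, with B baseline, P post-treatment score and G group. If P = a + τG + βB + error, then D = −a − τG + (1 − β)B − error. The group effect keeps its magnitude and p-value; only its sign reverses.

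**The case against.** **A reader might infer that the trial is underpowered.** The article does not support that. No correlation is given. Under the equal-SD assumption, power for the decrease meets 80% at any r from about 0.39 upwards, and above 0.5 the decrease is more precise than the unadjusted post-treatment score. This objection stands: what can be said is that the power is not established, not that it is too low.

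**The variance formulas rest on an unstated baseline SD.** This also stands in part. With unequal SDs the 0.5 threshold moves to s₀/(2s₁), and the power figures move with it. The comparison with ANCOVA survives: the decrease is never less variable, and it is equally variable only if the slope on baseline is 1.

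**The unadjusted test is not wrong, and covariates are often left to an analysis plan.** A t test on the decrease is valid under randomisation, so adjustment is a gain in efficiency and not the repair of a biased analysis. But section 2.8 does name the tests, and no later plan would make 2.2.1 and 2.5 refer to the same variable.

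**A reader might also infer that no baseline score will be taken**, because the schedule reads "Data were recorded by Case Report Forms (CRFs) during treatment (8 weeks, weekly) and follow-up (12 weeks, every 3 weeks". That does not follow. A decrease cannot be computed without a baseline, the sentence is a summary in a condensed article, and the flow diagram is not available here.

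**Conclusion.** The mismatch is explicit and certain: 2.2.1 is sized on one variable and 2.5 declares another. The stated 80% power is therefore not established for the primary outcome. The size and direction of the discrepancy are unknown, because they depend on r and on the baseline SD. Over r from 0 to 0.7, with equal SDs, equal expected baseline means and 107 analysed per group, power for the unadjusted decrease runs from about 59% to 98%.

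The loss of precision against ANCOVA depends much less on the unknowns. Under the same assumptions the unadjusted variance is 1.54 times the adjusted one at r = 0.3, 1.33 times at 0.5 and 1.18 times at 0.7, and ANCOVA power stays at 87% or more throughout. Validity is not in question. This is a point that should be changed because the remedy is nearly free, not one that would undermine the trial if left.

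**What to change.** In 2.5 and 2.8, make the primary analysis an ANCOVA of TNSS at the primary time point on treatment group, with baseline TNSS as covariate, and analyse RQLQ in the same way. The estimate may still be reported as a difference in decrease, since only its sign changes. This brings 2.2.1 and 2.5 into line, and the post-treatment SDs become a conservative basis for sizing, because the ANCOVA residual variance is (1 − r²) times theirs.

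If the unadjusted decrease is kept, restate the calculation in 2.2.1 with a justified SD of the decrease, for example from the preliminary experiment if baseline scores were recorded there. In either case the stated inputs should be reconciled with 107, since they give 88.

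The ANCOVA route costs a change of wording. It needs no extra patients or visits, because a decrease already requires a baseline score. Restating the calculation for an unadjusted decrease also needs no visits, but could change the required number in either direction.

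### The primary outcome, decrease in total nasal symptom score, names no visit, and the sample-size section only implies end of treatment and uses a score instead of a decrease

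*Protocol article*

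**What the plan says.** Section 2.5 (Outcome measures) states: "The main outcome indicator is the decrease of Total nasal symptom score". It gives no week, visit or summary over visits. The same paragraph gives the schedule: "Data were recorded by Case Report Forms (CRFs) during treatment (8 weeks, weekly) and follow-up (12 weeks, every 3 weeks".

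Section 2.2.1 (Participants source and sample size estimation) has the only hint of timing: "Sample size estimation will be based on post-treatment Total nasal symptom score". Its inputs are group means and SDs of a score: "the real EAP group was 2.82 ± 1.48, and the Sham EAP group was 3.47 ± 1.57".

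Section 2.8 (Statistical analysis) says "the hypothesis test was two-tailed test", with significance at P < .05. It offers an independent-samples t test or, where assumptions fail, a Mann–Whitney U test. It names no primary visit and no adjustment for baseline. The abstract says only that the nasal symptom score will be evaluated.

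**The concern.** A primary outcome needs a time point. Without one, an effect at the end of the 8-week course and an effect that persists 12 weeks later could each be reported as the primary result, although they are different claims. If the visit is settled only once the comparisons have been seen, the nominal 5% no longer describes the chance of a false positive claim of efficacy.

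The two sections also do not describe the same quantity. Section 2.5 has a decrease and section 2.2.1 has a score after treatment. These have different variances, so the sample size is not tied to the outcome as defined.

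**Working it through.** **Inputs**

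- From 2.5: weekly recordings for 8 weeks, then every 3 weeks for 12 weeks.
- From 2.2.1: 2.82 (SD 1.48) versus 3.47 (SD 1.57); α 0.05, power 0.80; 107 per group, raised to 134.
- From 2.8: two-sided test at 0.05.
- Not in the document: the correlation of TNSS change between visits. I assume 0.3 to 0.9.

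**The plan's own sample size**

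- Difference: 3.47 − 2.82 = 0.65.
- Pooled SD: √((1.48² + 1.57²)/2) = 1.526.
- n per group: 2 × (1.96 + 0.84)² × 1.526² / 0.65², which rounds up to 87 (88 with the t distribution). The stated 107 is not reproduced.
- Dropout allowance: 107/(1 − 0.20) = 133.75, so 134, which is reproduced.

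The gap between 87 or 88 and 107 is a separate matter, and nothing below depends on it.

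**Candidate visits**

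- All recordings: 8 + 12/3 = 12 (weeks 1 to 8, then 11, 14, 17 and 20).
- Post-treatment read loosely: week 8 plus four follow-up visits = 5.
- Post-treatment read as end of treatment: week 8 only = 1.

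**False-positive chance if any candidate visit may count, each tested at two-sided 0.05**

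Under independence the chance is 1 − 0.95^k. For k = 1 it is 0.05, for k = 5 it is 1 − 0.95⁵ = 0.23, and for k = 12 it is 1 − 0.95¹² = 0.46. Visits on the same person are correlated, so these are upper reference values. The correlated values come from 400,000 simulated sets of 12 normal test statistics under no effect:

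| Equal correlation (assumed) | Week 8 only | Week 8 + 4 follow-up | All 12 |
|---|---|---|---|
| 0.3 | 0.05 | 0.21 | 0.40 |
| 0.5 | 0.05 | 0.18 | 0.32 |
| 0.7 | 0.05 | 0.15 | 0.23 |
| 0.8 | 0.05 | 0.13 | 0.19 |
| 0.9 | 0.05 | 0.10 | 0.13 |

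If the correlation instead decays with time (first-order autoregressive, weekly correlation 0.3 to 0.9), the 12-visit figure is 0.45 to 0.26. Counting only results that favour real treatment, the 12-visit figure under equal correlation is 0.20 to 0.07, against a nominal 0.025.

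**Score versus decrease**

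Assume the same SD (1.526) at baseline and after treatment, with correlation ρ between the two. The SD of the decrease is 1.526 × √(2(1 − ρ)), and the residual SD after baseline adjustment is 1.526 × √(1 − ρ²).

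| ρ (assumed) | Score | Decrease | Baseline-adjusted |
|---|---|---|---|
| 0.3 | 1.53 | 1.81 | 1.46 |
| 0.5 | 1.53 | 1.53 | 1.32 |
| 0.7 | 1.53 | 1.18 | 1.09 |

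The SD used in 2.2.1 therefore equals that of the outcome in 2.5 only at ρ = 0.5. The baseline-adjusted SD is below both at each value shown.

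**The case against.** The best defence is that 2.2.1 does supply a time point. The article separates an 8-week treatment period from a 12-week follow-up, so post-treatment most naturally means the end of week 8, and it excludes weeks 1 to 7. On that reading there is one test at 5%. This largely stands as the natural reading, and it is why the 12-visit figures should not lead. It does not close the gap, because 2.2.1 names no week, does not define the outcome and describes a score instead of a decrease.

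A second defence is that a condensed article may leave detail to an analysis plan that is not shown. That holds for missing-data handling and the analysis set. It does not hold for the time point, which is part of the outcome definition that 2.5 itself sets.

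A reader might infer two stronger points that the document does not support:

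- *That 12 primary tests are planned.* Section 2.5 gives a recording schedule and 2.8 a type of test. Neither says the test is run at each visit. The schedule also refers to data in general, so TNSS at all 12 points is the natural reading but still an inference.
- *That the plan's handling of missing scores causes attrition bias.* The article describes no such handling. The 20% in 2.2.1 is a sample-size allowance, not a missing-data rule.

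A single unadjusted t test at a named visit would also hold the error at 5%. The case for baseline adjustment is precision, not error control.

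**Conclusion.** The point holds as a defect of definition: the primary outcome has no visit, the only hint of one is indirect, and the sample-size quantity differs from the outcome.

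The size depends on how the gap would be used. Read as end of treatment, the error is 5%. If the visit is picked after seeing results, it is about 10% to 21% over week 8 and the follow-up visits, and about 13% to 40% over all 12 visits, with 46% as the independence bound. The ranges rest on assumed equal correlations of 0.9 to 0.3, and a decaying correlation gives higher 12-visit values. The document does not say that such a choice would be made, but nothing in it rules one out. Because this concerns the main efficacy claim, it should be settled before any comparison by group is seen.

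**What to change.** - **2.5:** state that the primary outcome is the change in TNSS from baseline to week 8 (end of treatment), real versus sham, tested once at two-sided 0.05. Make the week-20 contrast a named secondary outcome for durability and the other visits descriptive.
- **2.2.1:** use the same quantity, giving the SD of the change or the post-treatment SD with the assumed correlation with baseline.
- **2.8:** for the primary outcome, replace the unadjusted test with a week-8 comparison adjusted for baseline TNSS. This can be ANCOVA, or the week-8 contrast of a mixed model on the weekly scores. With baseline as a covariate, ANCOVA of the score and of the change give the same group difference, so the mismatch no longer affects the test.

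The cost is a sentence in 2.5, a restated input in 2.2.1 and a replaced primary method in 2.8. No new visits or patients are needed, and a decrease already presupposes a baseline score. The downside is that a favourable result at another visit can no longer be called primary.
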